## Abstract

**Background:**

Agitation is common in the early stages of recovery from traumatic brain injury (TBI), when patients are in post-traumatic amnesia (PTA). Agitation is associated with risk of harm to patients and caregivers. Recent guidelines recommend that agitation during PTA is managed using environmental modifications. Agitation is also frequently treated pharmacologically, with the use of atypical antipsychotics such as olanzapine among the most common. This is despite a lack of well-designed studies to support the use of antipsychotics within this context. This study will be a double-blind, placebo-controlled randomised controlled trial. We will examine the efficacy, safety, cost-effectiveness and outcomes associated with the use of olanzapine for reducing agitation in patients in PTA following TBI over and above recommended environmental management.

**Methods:**

Fifty-eight TBI rehabilitation inpatients who are in PTA and are agitated will receive olanzapine or placebo for the duration of PTA. All participants will additionally receive optimal environmental management for agitation. Measures of agitation, PTA and health will be undertaken at baseline. Treatment administration will begin at a dose of 5 mg daily and may be escalated to a maximum dose of 20 mg per day. Throughout the treatment period, agitation and PTA will be measured daily, and adverse events monitored weekly. Efficacy will be assessed by treatment group comparison of average Agitated Behaviour Scale scores during PTA. Participants will cease treatment upon emergence from PTA. Agitation levels will continue to be monitored for a further 2 weeks, post-treatment measures of health will be undertaken and cognitive and functional status will be assessed. Level of agitation and functional health will be assessed at hospital discharge. At 3 months post-discharge, functional outcomes and health service utilisation will be measured.

**Discussion:**

This trial will provide crucial evidence to inform the management of agitation in patients in PTA following TBI. It will provide guidance as to whether olanzapine reduces agitation over and above recommended environmental management or conversely whether it increases or prolongs agitation and PTA, increases length of inpatient hospitalisation and impacts longer term cognitive and functional outcomes. It will also speak to the safety and cost-effectiveness of olanzapine use in this population.

**Trial registration:**

ANZCTR ACTRN12619000284167. Registered on 25 February 2019

## Background

The Australian Institute of Health and Welfare has reported a national traumatic brain injury (TBI) incidence of approximately 107 per 100,000 population per annum [1]. Productivity loss, economic costs and ongoing disability associated with TBI render this health condition a significant global public health concern [1–3]. Traumatic brain injury is frequently followed firstly by a period of coma and secondly by a period of post-traumatic amnesia (PTA). In moderate to severe TBI, PTA represents a period of recovery spanning days to months wherein the patient experiences generalised cognitive disturbance. This cognitive state is characterised by anterograde and retrograde amnesia, confusion, disorientation, attentional dysfunction, low arousal and poor awareness [4–7]. Patients in PTA often exhibit severe neurobehavioural symptoms [8–10]. Perhaps the most challenging of these is agitation, defined as an excess of behaviour involving restlessness, disinhibition and emotional lability [11–13]. When using a standardised measure of agitation, approximately one third of individuals exhibit agitation during the early stages of recovery from TBI [11, 14]. Agitation is problematic for patients, families and healthcare workers. Restlessness may lead to falls, and aggressive behaviour may result in self-harm, destruction of property and violence towards others [15, 16]. Agitation is associated with poorer rehabilitation engagement and longer hospital stays, and agitated patients reportedly exhibit poorer functional outcomes and less frequent return to private homes [8, 14, 17, 18].

Agitation may be managed using environmental modifications or pharmacological intervention. However, there is a clear lack of evidence to underpin the use of either of these approaches. A recent systematic review concluded that there exists a paucity of well-designed, adequately powered and controlled studies to support the use of pharmacological intervention for neurobehavioural symptoms during PTA, that clear evidence of efficacy for any pharmacological intervention is lacking and that no pharmacological treatment recommendations could be made [19]. This sentiment is echoed throughout the literature [7, 20–24]. Despite a lack of evidence supporting the efficacy and safety of any pharmacological intervention for agitation during PTA, the use of antipsychotics and anticonvulsants is common [12, 25, 26]. The use of newer atypical antipsychotics is preferred over older typical agents due to findings suggesting more favourable cognitive and motor outcomes associated with their use [27–30]. Such evidence is scant, and questions remain as to whether these agents are effective, and whether their use may have negative side effects such as increasing confusion, prolonging PTA duration and length of hospital stay and ultimately impairing recovery [27–35]. Further, it has been theorised that the administration of antipsychotic agents in TBI patients may impair arousal and cognition, exacerbating confusion, disorientation and drowsiness and in turn deepening PTA [7, 36]. Impairments in cognitive performance following TBI have been reported in animal models administered haloperidol [27–29, 35] and risperidone [27, 28, 35] but not olanzapine [29]. Additionally, antipsychotic administration was associated with prolonged PTA duration in several case series [32, 33, 37]. As improvement in cognition is thought to precede the resolution of agitation [5, 6, 26], the sedating effects of neuroleptics could potentially prolong PTA and serve to heighten or prolong agitation. In the face of such scant evidence, physicians are currently forced to rely on clinical experience, expert advice, low-level evidence and empirical assumptions of how similar conditions are managed in order to make treatment decisions, possibly risking poorer outcomes for patients and exposing staff and caregivers to risk of harm.

Olanzapine does not show demonstrated effects on cognitive function or recovery following TBI [29] and has a favourable safety profile when used to treat agitation in other conditions [38–41]. It is therefore arguable that olanzapine is suitable for treating agitation in the acute stages following TBI. Olanzapine is commonly prescribed during PTA [26]. There is however a complete lack of quality data regarding the efficacy, harms and other outcomes associated with the use of this drug for the treatment of agitation during the PTA period [19]. We have therefore chosen olanzapine as the active intervention for this placebo-controlled randomised controlled trial. Current evidence for the use of antipsychotics for the management of neurobehavioural symptoms during PTA is limited to case series with no formal comparison condition [19, 32, 42, 43]. Selection of a placebo comparator minimises bias and allows for collection of a higher level of evidence than that presently available. All study participants will receive optimal environmental management for agitation as per guidelines [7] and may receive a ‘rescue dose’ of olanzapine should agitation escalate to unmanageable levels. This permits the evaluation of olanzapine efficacy in conjunction with optimal environmental management over and above environmental management alone. Additionally, optimal environmental management allows for the ethical provision of medical care to this population in line with current guidelines [7] and the reduction of potential risks associated with agitation. The choice of a placebo-controlled design is therefore considered both scientifically rigorous and ethical.

The primary aim of this trial is to evaluate the efficacy of the atypical antipsychotic olanzapine in reducing agitation in patients in PTA following TBI over and above recommended environmental management. We hypothesise that patients who are administered olanzapine will show lower levels of agitation during PTA than those randomised to a placebo control group receiving optimal environmental management. The secondary aims of this research are to determine (1) the safety of olanzapine administration in PTA patients, whether olanzapine treatment: (2) reduces the number of clinically agitated days during PTA, (3) alters level of agitation at hospital discharge, (4) alters level of cognition in PTA, (5) alters PTA duration, (6) alters cognitive performance following PTA emergence, (7) alters length of inpatient hospital stay and (8) alters functional independence at discharge and 3-month follow-up. Finally, this research aims to evaluate the cost-effectiveness of olanzapine administration in PTA patients.

## Methods/design

This study will examine the efficacy of the atypical antipsychotic olanzapine in reducing agitation in patients in PTA following TBI. We will employ a parallel-group, double-blind, placebo-controlled, two-arm superiority randomised controlled trial with 1:1 allocation ratio. Participants will be 58 patients with TBI in PTA and experiencing clinically significant agitation recruited from the Acquired Brain Injury (ABI) Rehabilitation Unit at Epworth HealthCare, Richmond, Victoria, Australia. This private, not-for-profit urban hospital treats a significant proportion of patients with severe TBI in Victoria, Australia.

### Inclusion criteria

(1) Currently under hospital care at Epworth HealthCare for TBI rehabilitation, (2) a history of blunt head trauma with a loss of consciousness and an initial Glasgow Coma Scale of 3–14 and/or a period of PTA, (3) judged to be in PTA (score < 12) on the Westmead Post Traumatic Amnesia Scale (WPTAS; [44, 45]), (4) judged to be in a state of clinically significant agitation (score > 21) on the Agitated Behaviour Scale, (5) aged 18 years or older, (6) provision of signed and dated Medical Treatment Decision Maker Participant Information and Consent Form by the participant’s Medical Treatment Decision Maker (MTDM; during PTA) and (7) provision of signed and dated Participant Information and Continuing Consent Form by the participant (upon PTA emergence).

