### Exclusion criteria

(1) History of premorbid neurocognitive decline (e.g. dementia, stroke); (2) currently requiring antipsychotic treatment for psychotic illness; (3) current use of medications for agitation, including olanzapine, from which they are unable to be weaned; (4) pregnancy or lactation; (5) known allergy to olanzapine; (6) participation in another study involving an investigational product; (7) otherwise determined to be unfit for participation due to medical considerations.

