### Recruitment

Patients admitted to the Epworth HealthCare ABI Unit are routinely screened for PTA status using the WPTAS on admission. Those deemed to be in PTA have the WPTAS and ABS completed on a daily basis by a clinical neuropsychologist or nurse until they emerge from PTA. Study staff will be alerted to potential participants by ABI ward staff. Potential participants include patients in PTA who are exhibiting clinically significant agitation or thought likely to become agitated (due to factors such as agitation during acute hospitalisation). Due to their confusion and inability to lay down new memories, patients in PTA are not cognitively capable of consent. Recruitment will therefore target the patient’s MTDM. This will follow a two-stage process. Firstly, the study will be introduced to the patient’s MTDM by a member of their treating medical team and verbal consent for contact from study staff will be gained. Rapid consent processes are important to recruitment given the time-limited nature of PTA. The decision to introduce the trial to MTDMs of those patients determined likely to become agitated (rather than only those presently agitated) has been made in an effort to expedite the recruitment process and avoid exclusion of eligible participants. Agitation levels of those patients not presently agitated are monitored by study staff. If consent for contact is obtained and the patient is agitated at any stage during PTA, study staff will then contact the MTDM to carry out study consent procedures.

Participant recruitment commenced in June 2019, with the aim of recruiting participants until June 2022. Given that the full study protocol will have a duration of approximately 3 months, on average, data collection will continue until the end of September 2022. Epworth HealthCare treats more than 110 new patients with TBI annually, of whom 80 are likely to be in PTA on admission. Recent research studying this population within the Epworth HealthCare ABI ward [26] showed that 42.4% of TBI patients exhibited significant agitation according to the ABS whilst in PTA. Therefore, approximately 34 patients in PTA are likely to exhibit clinically significant agitation annually. Allowing for declined consent and ineligibility, we envisage recruitment of our sample over a 41-month period.

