### Screening

Study staff will be alerted to potential participants (in PTA according to the WPTAS and exhibiting or thought likely to exhibit agitation) by Epworth HealthCare ABI ward staff. Following consent procedures, a member of study staff or ABI unit medical registrar will screen this patient for study eligibility. Following confirmation of eligibility, the participant will be allocated the next available sequential participant number.

Some patients may already be taking medications for agitation, such as olanzapine, at this time. If they are deemed by study psychiatrists and the participant’s treating physician as able to be weaned off these medications, this will be done. Commencement of the study product may be carried out as participants are weaned off existing agitation medication, should this be deemed safe by study psychiatrists and the participant’s treating physician. In regard to current olanzapine use, commencement of study product may be initiated the following evening providing a dosage of no more than 10 mg per day has been administered in the last 24 h.

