### Participant timeline

The participant timeline is displayed in Table 1 schedule of activities.

**Table 1 Tab1:** Schedule of activities

Study phase	Screening/consent	Baseline/randomisation	Treatment period (PTA)	Post-PTA	Discharge	Three-month follow-up
ACD/ MTDM identification	X					
Trial introduction	X					
MTDM consent	X					
Screening	X					
Participant consent				X		
Randomisation		X				
Demographics^a^		X		X		
Medical record^b^		X	X		X	
Medical information^c^		X	X	X		
Blood test(s)^d^		X	X	X		
WPTAS		X	X			
ABS		X	X	X	X	
Simpson-Angus Scale		X	X			
Administer treatment			X			
Treatment log			X			
AE monitoring^e^			X			
RAVLT				X		
SDMT				X		
SF-12				X	X	X
FIM				X	X	
MPAI-4						X
PDHSUQ						X

^a^Age, gender, years of education, marital status, pre-injury employment/study status, drug and alcohol history, psychiatric history

^b^One or more of date and cause of injury, Glasgow Coma Scale, PTA duration, imaging results, surgical intervention, other injuries, Injury Severity Score, therapy hours and number of sessions, special nursing care, medication details, number of patients on ward

^c^Weight, BP, HR, WC

^d^Assessing fasting lipids, fasting glucose, HBA1C, creatinine

^e^Respiratory issues, lethargy, nausea, vomiting, difficulty swallowing, constipation, urinary retention, dizziness, seizures

#### Baseline—day 0

Following eligibility confirmation and randomisation, the following information will be gathered from the participant’s medical record: baseline WPTAS and ABS, demographic information (age, gender, years of education, marital status, pre-injury employment/study status, drug and alcohol history and psychiatric history) and medical information (date and cause of injury, Glasgow Coma Scale score, PTA duration, imaging results, surgical intervention, other injuries, injury severity score, therapy hours, special nursing care and medication details). Pre-treatment measures of weight, blood pressure (BP), heart rate (HR) and waist circumference (WC) will be conducted by nursing staff. Blood tests assessing fasting lipids, fasting glucose, haemoglobin A1c (HBA1C) and creatinine will be conducted. The Simpson-Angus Scale (SAS; [49]) will be completed by the patient’s treating physiotherapist, in order to assess the presence of extrapyramidal symptoms.

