### Statistical methods

#### Analysis of primary and secondary endpoints

Descriptive statistics will be reported using frequencies and percentages for categorical data. Percentages will be calculated based upon the number of patients for whom data are available. Continuous or dimensional variables will be summarised using means and standard deviations, with medians and interquartile ranges (difference between 25th and 75th percentiles) reported for potentially skewed data such as SF-12 PCS and MCS scores.

For the analysis of the primary endpoint, difference in mean daily ABS scores during PTA between olanzapine and control groups, a mixed model/multilevel regression framework [72], taking into account duration of PTA, will be employed. Although a difference between group means corresponding to a large effect size (0.80 of the pooled group standard deviation) is expected, a clinically significant improvement is defined as a difference in group means of the mean daily ABS scores within PTA equal to at least half a pooled group standard deviation difference, the minimal clinically important difference for improvement in irritable/aggression scale scores in TBI [68]. In regard to secondary endpoints, regression methods appropriate to the type of outcome variable will be employed. Comparison of the two groups on dimensional secondary endpoints such as ABS at discharge and WPTAS scores will be analysed using linear regression or median quantile regression. Median quantile regression, based upon the median and so less affected by very high or very low scores, will be employed for possibly skewed variables, such as SF-12v2 MCS and PCS scores, that may not meet the assumptions of linear regression [73].

Secondary endpoints involving count data including number of days in PTA, number of clinically agitated days, length of stay in hospital, agitation scores on discharge, number of “treatment failures” and number of AEs and other measures of treatment safety will be analysed using regression models for count data (Poisson or negative binomial regression as appropriate; [74]).

All statistical tests will be two-tailed, with alpha or statistical significance level set to *p* < 0.05. 95% confidence intervals will be reported throughout. The number of missing observations will be reported. Analyses will assume intention to treat, with all patients analysed as randomised.

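### The qualifying ABS may be scored while a patient is already on olanzapine, so the pooled primary contrast mixes starting the drug with continuing or withdrawing it

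*Protocol article*

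**What the plan says.** Inclusion criterion 4 requires the patient to be "judged to be in a state of clinically significant agitation (score > 21) on the Agitated Behaviour Scale". It sets no condition on medication at the time of scoring. Exclusion criterion 3 covers "current use of medications for agitation, including olanzapine, from which they are unable to be weaned", so a patient on olanzapine who can be weaned remains eligible.

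Under Screening, after consent, "a member of study staff or ABI unit medical registrar will screen this patient for study eligibility". The same section states: "Some patients may already be taking medications for agitation, such as olanzapine, at this time". Weaning is described after that, and study product may be started while it is under way. In current olanzapine users study product may start the following evening, subject to a limit on the dose given in the last 24 h. The Background describes olanzapine as commonly prescribed in PTA but gives no percentage.

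Under Recruitment, patients thought likely to become agitated can have the trial introduced to their decision maker early. They are then monitored, and if "the patient is agitated at any stage during PTA, study staff will then contact the MTDM" for consent.

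At baseline (Participant timeline) the ABS is taken from the medical record, together with "injury severity score, therapy hours, special nursing care and medication details". Randomisation is by permuted blocks with no stratification factor named. For the primary endpoint, "a mixed model/multilevel regression framework [72], taking into account duration of PTA, will be employed", and every daily ABS in the treatment period counts.

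**The concern.** For a patient already on olanzapine, the qualifying ABS partly reflects how well the test drug is working. The entry rule therefore selects on response to that drug: prior users held at 21 or below are not enrolled while they stay there, and prior users above 21 are.

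The two kinds of participant also face different contrasts. For a patient not on olanzapine at entry, the trial compares starting the drug with not starting it. For a patient already on it, the trial compares continuing under the trial schedule with being withdrawn to placebo. The primary aim is whether olanzapine reduces agitation in PTA over and above environmental management, which reads most naturally as the first contrast. The stated primary comparison averages the two. A small or null pooled result would then be hard to interpret, because it could mean that olanzapine does little or that part of the sample had already shown limited benefit.

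**Working it through.** **Step 1: reproduce the plan's figure.** Inputs from Sample size: standardised difference 0.80, SD 4.1 ABS points (so 0.80 × 4.1 = 3.28 points), power 0.80, two-sided alpha 0.05, attrition 10%. The two-sample t-test solution is 25.5, so 26 per group, with power 0.807 at n = 26. Then 26 / 0.90 = 28.9, so 29 per group and 58 in total. The plan's arithmetic is right.

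**Step 2: is the premise in the text?** Criterion 4 is silent on drug status. Criterion 3 keeps weanable users eligible. Screening places existing olanzapine use at the time of the eligibility check and weaning after it. No section asks for the ABS to be re-scored off drug. The premise holds.

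**Step 3: does selection change the effect?** This is an illustrative simulation, and every input except 4.1 and 3.28 is assumed. Off-drug ABS is normal with mean 22, 24 or 26 and SD 4.1. Individual drug response is independent of it, with mean 3.28 and SD 0, 1.5 or 3.0. A patient qualifies if the simulated on-drug score exceeds 21.5.

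| SD of response | Mean response among those qualifying on drug | Qualify off drug but not on drug |
|---|---|---|
| 0 | 3.28 | 29% to 55% |
| 1.5 | 2.64 to 2.96 | 29% to 52% |
| 3.0 | 1.20 to 2.13 | 32% to 50% |

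If response does not vary between patients, selection leaves the effect unchanged. If it varies and carries over into the trial, selection lowers it.

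**Step 4: effect on the pooled contrast.** Let f be the share of participants on olanzapine at the qualifying ABS and r the fraction of the planned effect they keep. Then d = 0.80 × (1 − f × (1 − r)). The documents give neither f nor r. t-test power at 26 per arm:

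| f | r = 0: d, power | r = 0.5: d, power |
|---|---|---|
| 0 | 0.80, 81% | 0.80, 81% |
| 10% | 0.72, 72% | 0.76, 77% |
| 20% | 0.64, 62% | 0.72, 72% |
| 30% | 0.56, 51% | 0.68, 67% |

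**Step 5: the opposing force.** Suppose prior users gain nothing from continuing, but those given placebo worsen on withdrawal by w SD. Then d = 0.80 × (1 − f) + f × w. At f = 30%, w = 0.50 gives d = 0.71 and power 71%. With w = 0.80 the pooled d is back at 0.80. With w = 1.0 it is 0.86, with power 86%. The net direction is therefore not fixed by the documents.

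**Step 6: chance imbalance.** At f = 30% with 29 per arm, treating allocation as simple randomisation, the between-arm difference in the share of prior users has SD √(0.3 × 0.7 × 2 / 29) = 0.12, or 12 percentage points.

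**The case against.** Several points on the other side stand.

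- **Internal validity.** Eligibility is settled before allocation and applies equally to both arms, so the randomised comparison is unbiased for the patients enrolled. The issue is which question it answers, and for whom.
- **Access.** A reader might infer that patients calm on olanzapine are never approached. Recruitment does not support that: patients likely to become agitated are identified early and monitored, and they can enter later.
- **Non-response.** An ABS above 21 on olanzapine does not show that the drug failed. The patient may have improved and still exceed 21, and exposure before entry may have been lower or shorter than the trial's titration range allows. Zero further benefit is therefore an extreme case, which is why the half-effect column is shown.
- **Direction.** A reader might infer that the result is necessarily pulled towards no effect. That requires response to vary between patients and earlier response to predict later response. Steps 3 and 5 show cases with no pull and with reversal.
- **The unseen SAP.** Covariates and supplementary analyses are ordinary SAP content, and the article says that an SAP will be prepared. Their absence from the article is not the fault. The point rests on the entry and screening rules, which the protocol fixes, and on the pooled primary comparison it states.

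The objection that a main-effect covariate cannot undo dilution is also correct, and the fix does not claim otherwise.

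**Conclusion.** The point holds as a matter of what is being estimated. The eligibility and screening text lets the qualifying ABS be scored on olanzapine with no off-drug re-score, so among prior users entry depends on response to the test drug. The pooled primary contrast may then not estimate the effect of starting olanzapine.

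The size cannot be computed from the documents. Under the assumed shares of 10% to 30%, the loss at 26 per arm runs from about 4 percentage points of power (81% to 77%: 10% share, half the effect kept) to about 30 (81% to 51%: 30% share, no effect kept). These figures assume dilution and ignore worsening on withdrawal, which could cancel or reverse it. Neither a biased randomised comparison nor a known direction of error is supported. The change is still worth making, because it is cheap and lets the trial separate the two contrasts.

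**What to change.** 1. From the baseline medication details already collected, derive a yes/no variable: on olanzapine at the qualifying ABS.
2. Add it as a covariate to the primary mixed model. This helps precision and deals with chance imbalance; it does not undo dilution.
3. Pre-specify a supplementary estimate of the primary contrast in participants not on olanzapine at the qualifying ABS, and report the treatment-by-prior-use interaction descriptively.
4. State with the results that the all-randomised estimate applies to patients agitated at entry, including some agitated despite olanzapine.
5. Reconcile Inclusion criteria, Exclusion criteria and Screening on whether the qualifying ABS is scored on or off existing agitation medication. Which it should be is for the investigators; no clinical rule is proposed here.

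The cost is one derived variable and some analysis-plan wording. Trial status reports 5 patients recruited, so pre-specification is still credible. The downside is precision: at a 30% share the supplementary estimate has about 0.7 × 26 ≈ 18 per arm and about 65% power at d = 0.80, so it should be read as supporting evidence and not as a second primary test.
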